## Abstract

**Background:**

Weight loss is challenging and maintenance of weight loss is problematic among midlife and older rural women. Finding effective interventions using innovative delivery methods that can reach underserved and vulnerable populations of overweight and obese rural women is a public health challenge.

**Methods/Design:**

This Women Weigh-In for Wellness (The WWW study) randomized-controlled trial is designed to compare the effectiveness of theory-based behavior-change interventions using (1) website only, (2) website with peer-led support, or (3) website with professional email-counseling to facilitate initial weight loss (baseline to 6 months), guided continuing weight loss and maintenance (7-18 months) and self-directed weight maintenance (19-30 months) among rural women ages 45-69 with a BMI of 28-45. Recruitment efforts using local media will target 306 rural women who live within driving distance of a community college site where assessments will be conducted at baseline, 3, 6, 12, 18, 24 and 30 months by research nurses blinded to group assignments. Primary outcomes include changes in body weight, % weight loss, and eating and activity behavioral and biomarkers from baseline to each subsequent assessment. Secondary outcomes will be percentage of women achieving at least 5% and 10% weight loss without regain from baseline to 6, 18, and 30 months and achieving healthy eating and activity targets. Data analysis will use generalized estimating equations to analyze average change across groups and group differences in proportion of participants achieving target weight loss levels.

**Discussion:**

The Women Weigh-In for Wellness study compares innovative web-based alternatives for providing lifestyle behavior-change interventions for promoting weight loss and weight maintenance among rural women. If effective, such interventions would offer potential for reducing overweight and obesity among a vulnerable, hard-to-reach, population of rural women.

**Trial Registration:**

ClinicalTrials.gov: NCT01307644

## Background

With obesity now considered an epidemic, multiple national initiatives are emphasizing the need to assist Americans in balancing healthful eating with regular physical activity [1-5]. The Strategic Plan for NIH Obesity Research emphasizes the need to include understudied rural populations and to design and test interventions using behavioral approaches to lifestyle change [6]. The Nurse's Health Study found evidence that adiposity in midlife is strongly correlated to a reduction in healthy outcomes among women when they reach age 70 [7].

Approximately two-thirds of midlife and older women in the USA are overweight or obese, with greater percentages (75%) of overweight and obesity reported among rural than among urban women [8]. Rural isolation may challenge rural women's development of healthy lifestyle patterns, as rural women may have differing eating patterns and increased barriers to physical activity [9,10]. While rural women have significantly higher rates of sedentary behavior and consumption of high fat diets, they are less likely to receive counseling in diet and activity or to be offered preventive measures than their urban counterparts [8,11]. This issue increases the importance of finding innovative ways to offer health and preventive services for this group.

Interactive web-based interventions for weight loss and maintenance have been shown to be effective in younger and middle-aged adults [12-16]. The proposed study is unique in targeting peri- and post-menopausal rural women whose health risks become magnified if they are overweight or obese [17,18]. Internet delivery of a behavior-change intervention to achieve weight loss and maintenance may be well received as middle aged and older women increasingly use the Internet as a supplemental source for health information [19,20].

Internet access is growing in rural communities, though rural residents may have fewer choices about the way they access the Internet and may have narrower bandwidth than urban residents [21]. Access to the Internet is available in 81% of households in the Midwestern state where this intervention is to be implemented [22]. Two separate pilot studies demonstrated that it was feasible to implement a behavior-change intervention using web delivery in midlife and older rural women [23,24]. We found that the majority of rural women enrolled in a web-based weight loss study were able to retrieve weight loss information from our intervention web-site and most participants said the web-based messages were helpful to them in trying to lose weight [24].

Studies using lifestyle modification for weight loss and weight maintenance suggest that 16 to 26 weeks is needed to achieve a loss of 5% to 10% of body weight, which is the percentage loss associated with health benefits [25-27]. The duration of weight maintenance interventions has been correlated with the likelihood of continued weight maintenance [28,29] as weight regain occurs within 1 to 2 years for most people. Based on this, we plan for a three phase intervention approach with phase 1 targeting weight loss (baseline to 6 months), phase 2 targeting guided continuing weight loss and maintenance (7-18 months), and phase 3 targeting self-directed weight maintenance (19-30 months). In prior work, we discovered that rural women were willing to participate in and remain committed to a 12-month behavior-change intervention using mailed newsletters and a 12-month follow up, with the attrition rate being 4.5% over 24 months [30]. Those women successfully adopted and maintained healthy eating and activity behaviors [30].

Website interventions have weight loss results as successful as in-person interventions, if not better [31,32]. A review of 21 technology-based studies identified self monitoring, counselor feedback, social support, use of a structured program and use of an individually tailored program, to be keys to short-term weight loss, with implications that these components may be helpful for long-term weight loss studies such as our study [33]. The major challenge with implementing web-based interventions is keeping participants engaged over the length of the study. Successful strategies have included an in-depth participant orientation [34] and planned reminder systems [31,34], methods that we will include in this study.

To achieve long-term weight maintenance, prolonged frequent in-person contacts are recommended [35]. Frequent contacts are typical of community weight loss programs; yet, such programming may not be feasible for rural women. One of the most common uses of the Internet is the exchange of information and support via peers, so using the Internet for peer-led support or professional email-counseling may be a viable option for providing frequent personal contacts necessary for long term weight maintenance [36]. Peer-led support groups in face-to-face formats were found to be effective in treatment of obesity [37,38]; however, no robust evidence was found for the effectiveness of peer-to-peer groups delivered by the Internet because some studies provided peer support by health professionals and other studies used complex interventions where it was not possible to separate the effects of the peer component [13,15]. In our 3-month pilot weight-loss study of rural women ages 50-69, we found that access to an interactive website plus a peer-led asynchronous support group enhanced weight loss [24].

Lifestyle modification interventions that provided continued contact with professional counselors were also found to be effective in achieving long-term weight loss maintenance [39]. Professional counseling for weight loss has been conducted using email. In two separate studies of overweight hospital employees and individuals at risk for type II diabetes, those in Internet education plus email professional counseling group lost significantly more weight than those in an Internet education only group after 6 months [12,15]. Varying results have been reported in achieving and maintaining weight loss in studies that incorporated weight loss counseling via email involving mostly midlife Caucasian women [13,15].

The literature is not clear whether web-based peer-support or professional email-counseling would be more advantageous methods for providing ongoing support for weight loss and maintenance. If peer-led online support groups are at least as successful in promoting weight loss and maintenance as individual professional email-counseling, the financial savings could be considerable.

This paper describes the protocol for a randomized controlled trial that aims to promote healthy eating and activity in order to achieve a targeted weight loss of 5% to 10% and weight maintenance among rural women ages 45-69 with a body mass index (BMI) of 28-45. To our knowledge, this study is the first to use a theory-based behavior-change intervention targeting midlife and rural women with an interactive web-based intervention for weight loss and weight maintenance, or to compare peer-led support to professional counseling.

### Aims and hypothesis

The primary aim is to compare the effectiveness of an interactive website only, interactive website plus a peer-led online support group, and interactive website plus professional weight loss counseling via email in facilitating initial weight loss (baseline to 6 months), guided continuing weight loss and maintenance (7-18 months) and self-directed weight maintenance (19-30 months). The secondary aim is to compare the 3 groups in improving healthy eating and activity behavioral and biomarkers.

We hypothesize that the groups who receive either peer-led online support or professional weight loss counseling will achieve better weight loss and weight maintenance outcomes than the group who receives interactive website only. There is insufficient evidence to hypothesize the relative effectiveness of peer-led online support and professional weight loss counseling.

## Methods/Design

### Ethics approval

The Institutional Review Board of the University of Nebraska Medical Center approved this study (approval number 23710-FB). Using the standardized and accepted protocol, written informed consent will be obtained from all participants prior to their enrollment.

### Study design

The study was designed as a randomized controlled trial and is summarized in Figure 1. Primary outcomes will be change in weight biomarkers and healthy eating and activity behavioral and biomarkers from baseline to subsequent assessments of 3, 6, 12, 18, 24, and 30 months. Secondary outcomes will be the percentage of women achieving at least 5% and 10% weight loss from baseline without regain, as well as achieving healthy eating and activity criterion standards at time points that correspond with the intervention phases (6, 18, 30 months). This study will be conducted in accordance with the Consolidated Standards of Reporting Trials (CONSORT) guidelines [40].

**Figure 1 F1:**
[figure not shown]
**CONSORT Participant Flowchart for the Women Weigh-In for Wellness Study**.

### Sample size

Sample size needed for the study was estimated for a test of group difference in response averaged across time using generalized estimating equations [41]. Calculations assumed a group mean difference of .45 standard deviations based on median values on these outcomes in [12,15] and our pilot work, two measurement times per phase, within-subject correlation ≤ .5, and α of .017 (Bonferroni adjustment for three pairwise comparisons). For the most conservative pairwise test that will be conducted, the two-sided comparison of the groups receiving counseling, 76 participants will be needed in each group. A total sample size of 306 will be recruited to allow for attrition of 25%, consistent with that experienced in both published weight loss studies and our own pilot work.

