### Data collection

Assessment of all variables will occur at baseline, 6 months, 18 months, and 30 months which correspond with the study phases. Women will be asked to attend a short assessment session at 3 months, 12 months, and 24 months which will include all measures except the Health Promotion Model cognitive-perceptual variables, blood glucose and lipids, self-reported diet, accelerometer data and estimated cardiorepiratory fitness via the 400-meter walk test. Established reliable and valid measures will be used for all assessments.

Questions pertaining to general demographic information and health history will be asked. The Patient-Reported Outcomes Measurement System (PROMIS-29 Profile v1.0) will be administered to obtain subscales of physical function, anxiety, depression, fatigue, sleep disturbance, social role, pain interference and intensity [49].

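### The 76 per group rests on two measurements per phase, but diet, accelerometer, glucose, lipid and 400-metre walk outcomes are measured once per phase and are still listed as primary at every visit

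*Protocol article*

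**What the plan says.** Under Sample size, the protocol article describes a calculation "estimated for a test of group difference in response averaged across time using generalized estimating equations". The inputs are a difference of .45 standard deviations, "two measurement times per phase, within-subject correlation ≤ .5", and "α of .017 (Bonferroni adjustment for three pairwise comparisons". The figure is set by what the section treats as the most conservative test: "the two-sided comparison of the groups receiving counseling, 76 participants will be needed in each group". Allowing for 25% attrition, 306 women are recruited. No power is given.

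Data analysis treats each phase separately, with average change from the start of the phase as the end point.

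Study design names as primary the change in weight biomarkers and in "healthy eating and activity behavioral and biomarkers from baseline to subsequent assessments of 3, 6, 12, 18, 24, and 30 months". The Abstract says the same in substance. Aims and hypothesis instead makes weight loss and maintenance the primary aim and puts the eating and activity markers under the secondary aim.

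Data collection schedules all variables at baseline, 6, 18 and 30 months. The visits at 3, 12 and 24 months are short sessions "which will include all measures except the Health Promotion Model cognitive-perceptual variables, blood glucose and lipids, self-reported diet, accelerometer data", and the 400-metre walk is omitted there too. The Physical activity section gives the same four time points for the accelerometer.

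**The concern.** A phase has two follow-up visits: 3 and 6 months, 12 and 18 months, or 24 and 30 months. An outcome measured at both gains precision from averaging, and the sample size uses that gain. An outcome measured only at the second visit has nothing to average. Because phases are analysed separately, another phase cannot supply the missing value.

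Two things follow. First, for diet, accelerometer, glucose, lipids and the walk test, 76 per group buys less than the Sample size section implies. Second, Study design promises changes in these outcomes at three visits where they are not measured. The cognitive-perceptual scales are also skipped at those visits, but they are behavioural determinants and not listed outcomes, so they do not enter this point.

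What is at stake is how null results are read. The article makes no directional prediction between peer-led and professional support. A non-significant difference between them on diet or accelerometer activity could be taken as better supported than it is.

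**Working it through.** **Inputs.** From Sample size: difference d = .45 SD; m = 2 measurements per phase; correlation ρ at most .5, with .5 used as the bound; two-sided α = .017; 76 per group; attrition 25%. Assumptions: power 80% (not stated), and the SD is that of a single measurement.

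**Formula.** For a difference averaged over m measurements,

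n per group = 2 (z₁₋α/₂ + z_power)² × [1 + (m − 1)ρ]/m ÷ d²

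with z₁₋α/₂ = 2.387 and z_power = .842, which sum to 3.228 (squared, 10.42).

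**Reproducing the plan (m = 2, ρ = .5).** The variance factor is (1 + .5)/2 = .75.
- n = 2 × 10.42 × .75 / .2025 = 77.2, so 78 per group against the stated 76.
- Power at 76: .45 × √(76/(2 × .75)) − 2.387 = 3.203 − 2.387 = .816, which is 79%.
- Attrition: 76/.75 = 101.3, so 102 per group and 306 in total, as stated.

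The match is close but not exact. Other pairs fit too: ρ = .3 with 85% power gives 76. At ρ = .5, two-sided 85% and 90% power give 87 and 100, which do not fit.

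**One measurement per phase (m = 1, nothing else changed).** The variance factor is 1.
- n for 80% power = 2 × 10.42 / .2025 = 102.9, so 103 per group.
- Power at 76: .45 × √(76/2) − 2.387 = 2.774 − 2.387 = .387, which is 65%.
- Detectable difference at 80% power: 3.228 × √(2/76) = .52 SD.

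Whatever power was intended, at ρ = .5 one measurement needs 1/.75 = 1.33 times as many women as two. Applied to 76, that is about 101.

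**Reading the two times as start and end of phase.** At ρ = .5 a change score has variance 2(1 − .5) = 1, so power at 76 is again 65%.

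**Sensitivity for the once-per-phase outcomes**

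| Condition | Power |
|---|---|
| Two-sided, 76 per group, no baseline adjustment | 65% |
| One-sided .017, 76 per group (z = 2.120; 2.774 − 2.120 = .654) | 74% |
| Two-sided, 92 per group (assumed 10% loss from 102) | 75% |
| Two-sided, 76 per group, baseline-adjusted, ρ = .5 (factor 1 − .25 = .75) | 79% |
| Two-sided, 102 per group (no attrition) | 80% |

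The baseline-adjusted figure depends on ρ: at ρ = .3 (factor 1 − .09 = .91) it is 70%.

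**The case against.** The strongest reply is that the calculation was made for weight, and for weight it fits. Weight is the primary aim, it is measured twice per phase, and sizing a trial on its main outcome is normal practice. That stands. A reader might infer that the trial as a whole is underpowered, or that 306 is too few; the article does not support either inference.

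A reader might also infer that the protocol claims 80% power and misses it. It states no power. The 80% is inferred from a near match, and ρ is given only as an upper bound.

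Nor does 65% cover every comparison. It belongs to the two-sided test of peer-led against professional support. The hypotheses against website only are directional, and Sample size singles out the two-sided test as the most conservative, so the other two may be one-sided, although the article does not say so. They would then have about 74%.

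Finally, 65% assumes the full planned loss and no baseline adjustment. The model's covariates are not given, and an article may leave them to the full plan. This also stands, and it is why a range is needed. It does not remove the point: adjustment and lower attrition would help the twice-measured outcomes as well, and the stated calculation relies on neither.

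Data collection does state the true schedule openly. That makes the visit list in Study design a wording error, but an error still.

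**Conclusion.** The point holds in limited form. The 76 per group is sound for weight and the other measures taken at both visits of a phase. It does not carry over to self-reported diet, accelerometer, glucose, lipids and the 400-metre walk, which the Abstract and Study design nevertheless include among the primary outcomes.

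For those outcomes, power for a .45 SD difference between peer-led and professional support is about 65%, given 80% intended power, ρ = .5, two-sided .017, 25% attrition and no baseline adjustment. It rises to about 74–80% under the more favourable conditions tabulated above.

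The conflict over visits, and the conflict between the aims and the outcome list, stand without any calculation.

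**What to change.** In the Abstract and Study design, make the once-per-phase outcomes secondary, in line with Aims and hypothesis, and list them at 6, 18 and 30 months only.

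In Sample size, state the intended power. Say that 76 per group applies to weight and other measures taken twice per phase. For the once-per-phase outcomes, give about 65% power or a detectable difference of about .52 SD, with the assumptions on sidedness, baseline adjustment, correlation and attrition.

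The cost is wording and a less favourable published figure. No participants or visits are added. Keeping these outcomes primary at 80% power on the same assumptions would instead need 103 per group, which is 138 after 25% attrition (103/.75 = 137.3) and 414 in total; that is not needed if they become secondary.

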#### Data analysis

The primary analysis will focus on each phase separately, testing planned pairwise comparisons of the intervention groups over time using generalized estimating equations (GEE). The primary end point will be average change in outcome from the beginning of each phase. GEE also will be used to test whether the groups differ over time in the proportion of women meeting 5% and 10% weight loss goals. Secondary analyses will include a trend analysis of differences in the pattern of change across the entire 30 months of the study. All primary analyses will be consistent with the intent-to-treat principle and imputation of missing values may be undertaken, depending upon the extent and pattern of missing data.

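### The only multiplicity rule named, plain Bonferroni at .017 for three pairwise tests, is valid but less powerful than Holm or the three-group closed test at the same .05 family-wise error

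*Protocol article*

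**What the plan says.** The Sample size section describes a calculation "estimated for a test of group difference in response averaged across time using generalized estimating equations". Its inputs are given as follows: "Calculations assumed a group mean difference of .45 standard deviations", with "two measurement times per phase, within-subject correlation ≤ .5" and an "α of .017 (Bonferroni adjustment for three pairwise comparisons"). It then says: "For the most conservative pairwise test that will be conducted, the two-sided comparison of the groups receiving counseling, 76 participants will be needed in each" of the arms compared. The total follows: "A total sample size of 306 will be recruited to allow for attrition of 25"%.

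The Data analysis section makes the pairwise comparisons the primary analysis in each phase, "testing planned pairwise comparisons of the intervention groups over time using generalized estimating equations (GEE"). It gives no significance level and no step-down, closed or gatekeeping rule. Bonferroni in the Sample size section is therefore the only adjustment the article names.

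The Aims and hypothesis section expects each supported group (peer-led, professional) to do better than website only, and states no direction between the two supported groups.

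**The concern.** With three groups, testing each pair at .017 leaves part of the permitted .05 error unused. If the three means are not all equal, at most one of the three pairwise nulls can be true. Once the global null has been rejected at .05, each pair can therefore be tested at .05 and the family-wise error stays at .05. This is a full closed test. Holm needs no global test and still improves on Bonferroni.

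The stake is the trial's main hypothesis, which concerns both supported groups against website only. If Bonferroni is carried into the analysis, the chance of showing both is lower than the same data and the same .05 family-wise error would allow.

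**Working it through.** **Inputs from the Sample size section.** Difference d = .45 SD; m = 2 measurements per phase; correlation ρ ≤ .5, taken as .5; α = .017 two-sided; 76 per group; attrition 25%. Power is not stated, so 80% is an assumption. Equal allocation (306/3 = 102 per group) is also assumed.

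**Reproducing the plan's figures.** For a time-averaged difference, the variance factor is (1 + (m − 1)ρ)/m = (1 + .5)/2 = .75, and

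n = 2 (z₁₋α/₂ + z_power)² × .75 / d² = 2 × (2.387 + .842)² × .75 / .2025 ≈ 77.2, so 78 per group.

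The plan states 76. With ρ = .45 the formula gives 75, so 76 fits 80% power closely. Power of 85% or 90% would need 87 or 100 per group, which does not fit. For the total, 76/.75 = 101.3, so 102 per group, and 3 × 102 = 306, an exact match.

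**Power per contrast under Bonferroni.** The standard error is √(2 × .75/76) = .1405 SD. The expected z is .45/.1405 = 3.203. Power is Φ(3.203 − 2.387) = .793.

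**Comparing procedures.** The three pairwise statistics were simulated jointly under a normal approximation, with group-mean variance .75/76. Two-sided tests, both supported groups .45 SD better than website only and equal to each other:

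| Procedure | Power per contrast | Power for both contrasts | Family-wise error, all means equal | Family-wise error, one true null |
|---|---|---|---|---|
| Bonferroni (.05/3) | .79 | .67 | .044 | .017 |
| Holm (.05) | .82 | .73 | .044 | .037 |
| Closed: 2-df test at .05, then pairs at .05 | .87 | .82 | .050 | .050 |

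Using .017 instead of .05/3 moves Bonferroni's power for both contrasts from .67 to .68, and its error with all means equal from .044 to .045. In this scenario the closed test reaches 80% power per contrast with about 64 per group, against 78 for Bonferroni.

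**Sensitivity** (Bonferroni, Holm, closed):

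- ρ = .3, two-sided, same means: power for both contrasts .76, .81, .88.
- One-sided tests against website only, ρ = .5: power for both contrasts .77, .82, .87.
- Equally spaced means 0/.225/.45 SD, ρ = .5, two-sided: power for the .45 SD difference .79, .80, .82; for each .225 SD difference about .22, .27, .35.

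**Does either alternative ever lose a rejection?** Holm never lost one against Bonferroni at .05/3. The closed test can. If the third mean lies midway between the other two, the 2-df statistic equals the pair's z². A pair with z² between 5.73 (the .05/3 cut-off; 5.70 at .017) and 5.99 (the 2-df cut-off) is then rejected by Bonferroni but stopped by the global test. With two-sided tests this happened in under 1% of simulated trials.

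**The case against.** **The .017 is a sizing input.** It appears among the assumptions of the sample size calculation, and the Data analysis section does not repeat it. A reader might infer that every pair will be tested at .017. The article does not say so, and an analysis plan that is not shown may refine the rule. This stands as a limit. What remains is that the article names one adjustment, ties it to the pairwise tests that will be conducted, and offers no other.

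**The power is not capped at 79%.** A reader might take 79% as the best the trial can do. The documents support the opposite reading: the correlation is stated as at most .5, so .5 is the least favourable value and 79% is the floor over that range, for two-sided tests with 76 per group. At ρ = .3 it is 85%. With all 102 per group and ρ = .5 it is 91%.

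**Some tests may be one-sided.** All three pairs share the same n, α and assumed difference. Calling the two-sided comparison of the supported groups the most conservative therefore suggests that the tests against website only are directional. This is not stated. If it is so, Bonferroni's power per contrast is already about .86, and the gain for both contrasts falls from about 15 points to about 10 for the closed test (.77 to .87) and stays near 5 for Holm (.77 to .82). The non-directional global test then also costs something: the chance of rejecting at least one pair falls from about .95 to .92.

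**Bonferroni has merits.** It is valid and simple, it gives matching simultaneous intervals directly, and its error is stricter than required when one null is true. It would be wrong to say that it brings no benefit, or that the closed test is better in every sample.

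**Conclusion.** The point holds as a matter of efficiency. The named adjustment controls the family-wise error, and nothing here suggests inflated type I error; 3 × .017 = .051 is rounding only, since the correlated tests give about .045.

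At the plan's least favourable inputs, Holm adds about 3 points of power per contrast and about 6 for showing both (.67 to .73). The closed test adds about 8 and 15 (.79 to .87, .67 to .82). These sizes assume 76 analysed per group, .45 SD, correlation .5, two-sided tests, both supported groups equally better, and a normal approximation. The gain depends on the configuration: with equally spaced means Holm adds only about 1 point for the largest difference. A gain for showing both contrasts remained at the lower correlation and with one-sided tests against website only.

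**What to change.** Keep .017 as the conservative sizing assumption; the sample size does not change. Add one sentence to the Data analysis section, fixed before any unblinded analysis, stating that for each outcome and phase the three pairwise tests use one of these:

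- Holm at family-wise .05, starting from exactly .05/3 and not the rounded .017, so that no Bonferroni rejection at .05/3 is lost; or
- the closed procedure: the 2-df GEE group test at .05 and, if it is significant, each pair two-sided at .05.

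The same sentence should say whether the tests against website only are one- or two-sided. If they are one-sided, Holm is the simpler choice, because the 2-df global test is not directional.

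The costs are small. Matching simultaneous intervals are less direct, so the plan should say which intervals will be reported (Tukey-type, or plain 95% intervals labelled as unadjusted). The closed test can occasionally stop a pair that Bonferroni would reject. The change covers the three pairs for one outcome in one phase; multiplicity across the three phases and the several primary outcomes needs its own statement.
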